## Method

### Study design

We will conduct a non-blinded, randomized, controlled, parallel-group, superiority trial comparing (i) TBT-S plus TAU to (ii) TAU only. Similar control conditions have been used in previous trials of short-term interventions for eating disorders (e.g., Godart et al., 2012; Gowers et al., 2010; Quiles et al., 2025). Four main assessments will be conducted: pre-assessment, post-assessment, and 3- and 12- months follow-up. Eating disorder service utilization during the preceding 3 months will be assessed at pre-assessment and at 3-, 6-, 9-, and 12-months follow-ups. See Figure 1 for Consolidated Standards of Reporting Trials (CONSORT) flow chart (Hopewell et al., 2025) of the trial. The project will be arranged as a multisite study with two collaborating units (Regional department for eating disorders (RASP) at Oslo university hospital and the Department of eating disorders (RAS) at Haukeland university hospital). The collaborating clinics offer TBT-S as part of their standard clinical practice. In accordance with the treatment manual (Hill et al., 2022) there are no requirements regarding the specific time point during the ongoing treatment at which TBT-S should be introduced; clinicians can integrate TBT-S flexibly into ongoing therapy. Thus, the timing of TBT-S within TAU is individualized rather than standardized and depends primarily on practical considerations, including participants’ ability to take time off for the 5-day intervention and the scheduling of TBT-S weeks at the treatment sites (4–6 times per year). Multiple participants are assigned to each TBT-S week before being randomized to receive TBT-S plus TAU or TAU only. Participants randomized to TAU only complete assessments at the same time-points as those randomized to the corresponding TBT-S week, ensuring comparability across study arms.

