### Interventions

#### Temperament based therapy with support (TBT-S)

Participants in the intervention arm will receive 5 days of TBT-S in addition to ongoing TAU. TBT-S is administered to three to six adults with AN/AAN together with up to four supports each. As described in the TBT-S treatment manual (Hill et al., 2022), the treatment structure consists of five consecutive days of treatment, up to seven h each day. TBT-S is delivered in a multifamily format where both individuals with AN/AAN and supports are included in all the following five treatment strategies: (1) *Neurobiological psychoeducation*. Psychoeducation helps participants recognize how AN could be understood as a biologically influenced illness, emphasizing temperament traits (e.g., anxiety, harm avoidance, altered reward processes) and mechanisms that may be involved in maintaining eating disorder symptoms; (2) *Experiential learning activities addressing eating disorder neurobiology and traits*. The experiential activities are developed to aid participants experience how traits such as cognitive inflexibility can be experienced, how to maneuver toward recovery and how supports can be of help and, importantly, they help provide insight through action rather than discussion alone; (3) *Client and support skills training*. The skills training aspect of TBT-S teaches practical, trait-aligned tools to respond more effectively to eating disorder behaviors and to ensure consistent use of skills for recovery in daily life; (4) *Meal coaching*. Participants practice skills in real time together with supports and clinicians to help tolerate distress, reduce rituals and reinforce adaptive behaviors pre, post and during meals; (5) *TBT-S behavioral agreement*. The behavioral agreement is an individually tailored written plan, developed collaboratively by the participant with AN/AAN, their supports and the clinical team. It clearly outlines recovery-related behaviors and the role of supports. The agreement should help with accountability and provides a structure to facilitate consistent implementation of treatment strategies (Hill et al., 2022). Drop-out rates will be tracked systematically. We have previously translated and adapted the TBT-S material to Norwegian and assessed its feasibility and acceptability with Norwegian participants (Stedal et al., 2023).

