### Sample size calculation

The sample size calculation is conducted based on the primary outcome, global EDE-Q score at 3-month follow-up. It is informed by data from a feasibility study conducted by the authors (Stedal et al., 2023), in which the *SD* of the change in global EDE-Q from baseline to post-treatment was 0.87. A between-group difference in global EDE-Q change of 0.44 was assumed, based on the study by Tregarthen et al. (2019), who defines 0.5*SD as a clinically relevant difference in change from baseline, corresponding to a medium effect size (Cohen’s *d* = 0.5). In a two-sided test of superiority with *α*-level = 0.05 and 80% power, a total sample size of 126 is required. Participants are allocated to study arms in a 1:1 ratio. To account for the observed correlation (*p* = 0.732) between baseline and 3-month follow-up as reported in our previous feasibility study (Skoog et al., 2025), an ANCOVA framework is employed in the sample size calculations using raw EDE-Q global score at 3-month follow-up while adjusting for baseline. Thus, the number of participants is multiplied by the factor (1 + *p*)/2. Applying the correlation *p* = 0.732, the multiplicative factor is (1 + 0.732)/2 = 0.866. This results in an estimated required sample size of 110 participants. Assuming 10% attrition rate, we will include a total of 120 participants.

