### Statistical analysis

Primary analyses will be conducted on the *Full Analysis Set* (FAS), defined as all participants who were randomly assigned to a treatment arm and who provided, at minimum, the following pre-assessment data; for individuals with AN/AAN, the EDE-Q; and for supports, at least one completed questionnaire, irrespective of the measure. As a sensitivity analysis for the primary outcome, the primary endpoint analysis will also be conducted on the *Per-protocol* (PP) population. In the TBT-S + TAU arm, the PP population will comprise those in the FAS who attended at least four of the five TBT-S days. In the TAU arm, the PP population will be identical to the FAS, as no additional intervention is delivered. Per protocol analyses will be adjusted for the time interval between randomization and pre-assessment.

The superiority of TBT-S plus TAU over TAU alone for the primary outcome will be analyzed using a linear mixed model with the 3-month EDE-Q global score as a continuous outcome, with baseline EDE-Q, treatment arm and study site, Time (factor) and Time (factor)*treatment arm interaction as fixed effects and subject ID as random effect. Secondary outcomes will be analyzed using linear mixed models in which baseline value, treatment arm, study site, time and time*treatment arm-interaction are included as fixed effects, and subject ID is included as random effect. The use of mixed linear models will allow for including in the analyses also participants that do not complete all assessments. As participants in the TAU alone condition may opt to receive the intervention after their 3‑month assessment, a proportion of TAU alone participants will undergo post‑3‑month treatment crossover. Analyses that include 6‑, 9‑, or 12‑month follow‑up will therefore incorporate analytic strategies appropriate for partial crossover. Further details of the statistical analyses will be specified in a statistical analysis plan, which will be completed before the database is locked and analyses commence.

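### TBT-S is delivered in groups of three to six, but the sample size and models treat participants as independent; any positive within-group correlation makes the standard error too small and the 80% power too optimistic

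*Protocol article*

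**What the plan says.** On delivery, the TBT-S part of the Interventions section says: "TBT-S is administered to three to six adults with AN/AAN together with up to four supports each". The five treatment components, meal coaching among them, are shared within that group. Study design adds: "Multiple participants are assigned to each TBT-S week before being randomized to receive TBT-S plus TAU or TAU only". The week is therefore known for every participant before allocation.

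On the sample size, the protocol article states: "A between-group difference in global EDE-Q change of 0.44 was assumed". The standard deviation comes from the feasibility study, where that of the "change in global EDE-Q from baseline to post-treatment was 0.87". It continues "In a two-sided test of superiority with *α*-level = 0.05" and "80% power, a total sample size of 126 is required". A baseline-correlation factor of 0.866 is then applied: "This results in an estimated required sample size of 110 participants". Allowing for 10% attrition, 120 are to be randomised 1:1. No ICC or design effect appears at any step.

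On the analysis, the primary model has baseline EDE-Q, arm, site and time as fixed terms, and "Time (factor)*treatment arm interaction as fixed effects and subject ID as random effect". The secondary models have the same structure. The limitations in the Discussion do not mention clustering.

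**The concern.** Members of one TBT-S week share a clinical team, meals and one another for five days, while controls have no comparable shared exposure. This is a partially nested design: clustering caused by treatment can arise in one arm only. The protocol itself points to possible mechanisms. It rates TBT-S weeks for fidelity and therapist competence, and it names peer support among the non-specific elements that might explain a benefit.

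A subject random effect deals with repeated measures on one person, not with correlation between people. The fixed site effect does not absorb the correlation either, because TBT-S weeks are run repeatedly (four to six times a year).

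The error runs in one direction. Any positive ICC makes the confidence interval too narrow and favours a finding of superiority. In the first controlled trial of this therapy, a positive primary result could be challenged on this point.

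**Working it through.** **The plan's own figures.** Two-sided α = 0.05, power 80%, difference 0.44, SD 0.87.
- A t-test with 0.44/0.87 gives 63 per arm, 126 in total; the normal formula with d = 0.5 also gives 126.
- 126 × 0.866 = 109.1, rounded up to 110.
- 120 × 0.9 = 108 analysed, or 54 per arm.
- Residual SD after baseline adjustment = 0.87 × √0.866 = 0.810. SE under independence = 0.810 × √(2/54) = 0.156. Power is 79.9% (t-based) or 80.6% (normal approximation).

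The stated figures are thus reproduced under independence, and at 108 analysed there is no reserve.

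**Assumptions needed.** The ICC is not in the document; I take 0.01, 0.05 and 0.10, meaning the correlation left after baseline adjustment. Group size m = 4.5 is the midpoint of three to six, so 54/4.5 = 12 groups.

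**Formulas.**
- Design effect in the TBT-S arm: DE = 1 + (m − 1) × ICC.
- Variance inflation of the arm contrast: (1 + DE)/2, because only one arm is clustered.
- Type I error of the model as written: 2 × [1 − Φ(1.96/√inflation)].
- Power of a corrected analysis: non-central t with SE = 0.156 × √inflation.
- Satterthwaite df: (DE + 1)² / (DE²/11 + 1/53). At ICC 0.05 this is 2.175² / (1.175²/11 + 1/53) = 4.731/0.1444 = 32.8.

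| ICC | DE | Inflation | True SE / model SE | Type I error, model as written | Corrected power, 106 df | Satterthwaite df | Corrected power, Satterthwaite |
|---|---|---|---|---|---|---|---|
| 0.01 | 1.035 | 1.0175 | 1.01 | 5.2% | 79.2% | 35.6 | 77.7% |
| 0.05 | 1.175 | 1.0875 | 1.04 | 6.0% | 76.5% | 32.8 | 74.8% |
| 0.10 | 1.350 | 1.175 | 1.08 | 7.1% | 73.3% | 29.9 | 71.3% |

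**Check by simulation.** The analysis without a group term was simulated 40,000 times, with 54 per arm and 12 TBT-S groups of four or five. Type I error was 5.9% at ICC 0.05 and 7.0% at ICC 0.10, in line with the formula. With the true difference at 0.44, the same analysis rejected 79.4% and 78.3% of the time. The model as written therefore keeps most of its nominal rejection rate, but with an inflated type I error. The lower powers in the table belong to an analysis that controls the error.

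**Smaller analysed groups.** Ten per cent attrition within groups gives m = 4.5 × 0.9 = 4.05. At ICC 0.05, m = 4.05 gives inflation 1.076, type I error 5.9% and power 77.0% (106 df). With m = 3.6 the figures are 1.065, 5.8% and 77.4%.

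**The case against.** The best defence is that the effect may be very small. Shared exposure lasts five days and the endpoint comes three months later. Participants continue their own varied usual treatment, and delivery is manualised and rated for fidelity. All of this could keep the ICC low, and at 0.01 the consequence is negligible. This stands, and it is why the size has to be given as conditional.

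The analysed group size may also be below 4.5. If four to six weeks a year is the total across sites, inclusion from December 2024 to December 2027 gives 12 to 18 weeks, and 60 TBT-S participants over those weeks is 3.3 to 5 per group before attrition. This also stands; it shrinks the effect without removing it.

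A third defence is that the protocol leaves further details to a statistical analysis plan. This answers only in part. The random-effects structure and the sample size are already stated, so a group term would change the published model rather than fill in a detail.

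A reader might infer three stronger things that the document does not support:
- That the standard error is certainly too small. This needs a positive ICC, which is plausible but not documented.
- That the whole trial suffers the full design effect. Treatment-induced clustering is in one arm, so the contrast is inflated by (1 + DE)/2. A week effect common to both arms would not bias the standard error downward.
- That power is near 71% and type I error near 8%, the figures for ICC 0.10 with six analysed in every group. That combines the highest assumed ICC with the maximum group size and no attrition within groups.

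**Conclusion.** The point holds as a conditional one. The protocol describes group delivery, and neither its sample size nor its stated models allow for it. The omission is clear from the text; its size is not, because it depends on an assumed ICC and on the number analysed per group. Over ICC 0.01 to 0.10 at 4.5 per group, type I error of the model as written runs from about 5.2% to 7.1%. Power with valid error control runs from about 79% to 73%, or about 78% to 71% with small-sample degrees of freedom. A central case of ICC 0.05 means an error rate near 6% and power near 75 to 77%. That is modest to moderate and always in favour of the new treatment. I rate it as something that should be fixed, not as a flaw that undermines the trial: endpoint, eligibility and data collection are untouched.

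**What to change.** Keep the TBT-S week or group identifier in the analysis data set. Before database lock, specify for the primary and secondary models a random effect for TBT-S group in the TBT-S arm only (a partially nested model), with arm-specific residual variance and Satterthwaite or Kenward-Roger degrees of freedom. A week effect shared by both arms is optional and not needed for validity.

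Replace the unqualified 80% with the power of 120 randomised over a stated ICC range, for example 0.01 to 0.10, computed with the same degrees-of-freedom method as the analysis. Say that the ICC is an assumption.

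The cost is a change of wording in the protocol and analysis plan, a stated power several points lower, and about 30 to 35 degrees of freedom instead of about 106. Week allocation already exists, so no new data are needed. With 31 participants randomised at manuscript submission and inclusion planned to December 2027, the change can still be prespecified.

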### Measurements

Table 1 provides an overview of interviews and self-report assessments at the different time points. Within 14 days before the start of a TBT-S-week, clinician-administered interviews will be conducted, and pre-assessment forms will be completed in both treatment arms. Post-assessments will be completed within 12 days after the last day of the TBT-S week and follow-up assessments within a 20 day period centered at 3-, and 12 month follow-ups. Use of health care services will be assessed at pre-assessment and at 3-, 6-, 9-, and 12-months follow-ups. The primary endpoint will be the group difference in change in eating disorder psychopathology (Eating Disorder Examination Questionnaire [EDE-Q (Fairburn and Beglin, 1994)] Global score) from pre-assessment to 3- month follow-up. The Norwegian version of EDE-Q has shown satisfactory psychometric properties (Rø et al., 2015; Reas et al., 2011). Interviews performed at pre-assessment are the Mini International Neuropsychiatric Interview [M.I.N.I. 7.0.2 (Sheehan et al., 1998)] and the Eating Disorder Assessment for DSM-5 [EDA-5 (Sysko et al., 2015; Dahlgren et al., 2020)] which are administered to assess comorbidities and confirm the AN/AAN diagnosis self-reported by the patient. When travel time to the main recruitment site (Oslo university hospital) allows for in-person assessments, participants are invited to fill out the forms on site, where weight and height will also be measured and registered. All other participants will complete the self-report assessments remotely and self-report weight and height. The M.I.N.I. and EDA-5 interviews of these patients will be conducted via a secure digital video platform. The main tools used for assessment are all previously validated and well-established measures (Akoury et al., 2018; Bouwmans et al., 2013; Cejalvo et al., 2025; Dambi et al., 2018; Feng et al., 2021; Fowler et al., 2014; Gratz and Roemer, 2004; EuroQol Group, 1990; Hibbs et al., 2014; Hoefman et al., 2013; Håseth et al., 1990; Osman et al., 2012; Pedersen et al., 2022; Sepulveda et al., 2009; Spielberger, 1970; Timman et al., 2015; Wiedemann et al., 2002; Winkler et al., 2019). Utilization of health care services and data on resource use will be collected using the self-reported Treatment Inventory of Costs in Patients with psychiatric disorders (TIC-P) questionnaire (Bouwmans et al., 2013; Timman et al., 2015). To ensure a detailed characterization of TAU, additional items on eating disorder service utilization have been added. These include whether the participant is currently receiving ED treatment, level of care and treatment intensity, as well as type of therapy and treatment modality. This information on service utilization together with the EuroQoL 5D [EQ-5D (Feng et al., 2021; Group, 1990)] and the Care-related Quality of Life instrument [CarerQol-VAS (Cejalvo et al., 2025)] will be used to assess the potential cost-effectiveness of TBT-S. Cost will be examined from both the healthcare provider as well as the societal perspective. Norwegian translations of all measures will be used. Two of the measures (Accommodation and Enabling Scale for Eating Disorders and Eating Disorder Quality of Life Scale) have not been validated in Norwegian. TBT-S attendance will be assessed at post-assessment (TBT-S plus TAU group only) using a study specific question added to the Client Satisfaction Questionnaire, asking participants to report how many of the five TBT-S treatment days they attended. At the 3- and 12- month follow-ups, adherence to TBT-S treatment recommendations will also be assessed using self-report measures, including the extent to which participants who received TBT-S have utilized the treatment tools provided during the treatment week.

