The study has some potential limitations which are worth noting, some of which could impact the ability to interpret potential improvements. For example, the participants in the TBT-S arm will receive 35–40 h of additional treatment which is not controlled for in the control group. Thus, it will be uncertain if any improvements in the TBT-S group could be attributable to the increased dose of treatment, and/or non-specific elements in the TBT-S group (e.g., placebo, peer-support, behavioral activation). Nevertheless, this RCT marks an important first step in deciphering whether TBT-S in addition to TAU could improve treatment outcomes, and future studies might wish to include a comparison group program of similar intensity, with as little overlap as possible with TBT-S, thereby increasing the chances of better attributing any changes to TBT-S. Further, being allocated to TAU could be discouraging for some participants, increasing the risk of drop-out for this group. In addition, currently there are no other clinics in Norway offering adult TBT-S for AN/AAN. However, this could change over time and there is a risk that the TAU group gets tainted by TBT-S from a treatment provider not included in the study. Travel costs are covered through, a public service that reimburses travel expenses for healthcare treatments and clinical trials, and most employers will provide either paid or unpaid leave to receive healthcare. However, some eligible participants may still be prevented to participate in the study because they are not able to take time off work to attend TBT-S. Furthermore, the power analysis were based on our feasibility study with a comparable population. Even so, since both groups in this RCT will be receiving active treatments, there is a risk that potential differences between groups could be obscured by varying treatment settings and intensities, which would be expected to achieve reasonable effect sizes on their own. In addition, the timing of TBT-S within participants’ ongoing treatment is not standardized. As TBT-S is designed to be flexibly integrated into routine clinical care, participants may receive the intervention at different points in their treatment trajectory, which could contribute to heterogeneity in treatment response and introduce potential floor or ceiling effects. Finally, the lack of baseline assessment before randomization could result in the study’s pre-assessment being biased by the randomization. We will perform analyses of pre-assessments to check that the randomization produced equivalent groups. Any differences will be controlled for.

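### The mixed models impose one baseline slope on all follow-up visits; a baseline-by-time term would adjust each visit more fully (minor)

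*Protocol article*

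**What the plan says.** The protocol article, section Statistical analysis, lists the fixed effects of both models. For secondary outcomes, "baseline value, treatment arm, study site, time and time*treatment arm-interaction are included as fixed effects", with a random subject effect. The primary model has baseline EDE-Q, arm and site, plus "Time (factor) and Time (factor)*treatment arm interaction as fixed effects and subject ID as random effect". Neither list has a baseline-by-time term.

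The visits are far apart. In Measurements, "Post-assessments will be completed within 12 days after the last day of the TBT-S week", and the last visit is at 12 months. Table 1 has EDE-Q, CIA, STAI and DERS-SF at post, 3 and 12 months. BMI and several other scales are taken at 3 and 12 months only.

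Three further statements bear on the point:
- Analyses that include 6, 9 or 12 months will "incorporate analytic strategies appropriate for partial crossover".
- "Further details of the statistical analyses will be specified in a statistical analysis plan".
- The Discussion concedes that the pre-assessment follows randomization and could be biased by it, and adds: "Any differences will be controlled for".

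**The concern.** A baseline main effect without a baseline-by-time term forces the same regression on baseline at every visit. That is right only if baseline predicts the outcome equally well at all of them. Prediction usually weakens with time, and here the gap runs from under two weeks after the treatment week to a year. The sample size calculation itself uses a visit-specific value, the correlation "between baseline and 3-month follow-up as reported in our previous feasibility study".

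Where a visit's own slope differs from the common one, part of any baseline difference stays in the arm effect and the estimate is less precise than it could be. In most trials such a difference is only chance. Here the protocol allows that it may be systematic and says it will be controlled for, so incomplete adjustment matters somewhat more.

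**Working it through.** **The plan's own figure.** "In a two-sided test of superiority with" a 5% level and 80% power, a difference of 0.44 and an SD of change of 0.87 give 126 in total by the t-test (124 by the normal approximation). The ANCOVA factor is (1 + 0.732)/2 = 0.866, and 126 × 0.866 = 109.1, stated as 110. With 120 randomized and 10% attrition, 108 complete. The sample size concerns one visit and does not depend on this point.

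**Formula.** Take unit SDs, complete data and a random intercept. Let r_t be the baseline correlation at visit t. The single baseline coefficient then estimates the mean b of the r_t. At visit t:
- share of a baseline difference left in the arm effect = r_t − b;
- variance relative to a visit-specific slope = 1 + (r_t − b)² / (1 − r_t²).

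**Inputs.** Only r = 0.732 (EDE-Q, 3 months) is in the document. All other correlations are assumptions, shown as ranges.

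**Case A: post, 3 and 12 months in one model.**

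| r at post / 3 / 12 months | b | Share left at post / 3 / 12 months | Variance ratio at post / 12 months | SE loss at post / 12 months |
|---|---|---|---|---|
| 0.80 / 0.732 / 0.60 | 0.711 | +9% / +2% / −11% | 1.02 / 1.02 | 1% / 1% |
| 0.85 / 0.732 / 0.50 | 0.694 | +16% / +4% / −19% | 1.09 / 1.05 | 4% / 2% |
| 0.90 / 0.732 / 0.40 | 0.677 | +22% / +5% / −28% | 1.26 / 1.09 | 12% / 4% |

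Worked example, middle row: b = (0.85 + 0.732 + 0.50)/3 = 0.694. At post, 0.85 − 0.694 = 0.156, and 1 + 0.156²/(1 − 0.85²) = 1 + 0.0243/0.2775 = 1.088. At 3 months the SE loss is 0.3% or less in every row. Simulated variance ratios (110 patients, 3,000 trials per scenario) were 1.02, 1.09 and 1.25 at post and 1.02, 1.05 and 1.08 at 12 months, which agrees with the formula.

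For scale, suppose a pre-assessment difference of 0.3 EDE-Q points (hypothetical). It leaves 0.3 × 0.09 to 0.3 × 0.22 = +0.03 to +0.07 at post and −0.03 to −0.08 at 12 months, against the planned 0.44.

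**Case B: 12 months modelled separately because of crossover.** Only post and 3 months share a slope.

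| r at post / 3 months | b | Share left at post / 3 months | SE loss at post / 3 months |
|---|---|---|---|
| 0.80 / 0.732 | 0.766 | +3% / −3% | 0.2% / 0.1% |
| 0.85 / 0.732 | 0.791 | +6% / −6% | 0.6% / 0.4% |
| 0.90 / 0.732 | 0.816 | +8% / −8% | 1.8% / 0.8% |

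The same 0.3-point difference would move the primary contrast by −0.01 to −0.03.

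**Measures taken only at 3 and 12 months, BMI-like.** If pooled with r = 0.92 / 0.65, then b = 0.785, ±13.5% is left, and the 3-month variance ratio is 1 + 0.135²/(1 − 0.92²) = 1.12 (SE loss about 6%). With 0.90 / 0.75 the loss is 1.5%; with 0.97 / 0.70 it is 14%. In Case B one follow-up visit remains, there is no common slope, and the loss is zero.

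**Reported intervals.** Restricted maximum likelihood fits were simulated with 54 per arm and 1,500 runs per model. For BMI-like 0.95 / 0.70, the true SD of the 3-month effect fell from 0.068 to 0.061 when the interaction was added, and the share left fell from 12.7% to about 0. The average reported SE fell only from 0.109 to 0.107, because a random-intercept model has one residual variance for all visits. Mean estimates were about 0 with and without the term, so there is no average bias when baselines are balanced.

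**The case against.** The strongest reply is that the article defers details to a statistical analysis plan that is not shown, and that a baseline-by-time term is such a detail. This stands in part. That plan may add the term, and nothing in the article excludes it. But the article does not leave the fixed effects open: it lists them and names one interaction with time but not the other. A plan that follows the list keeps the restriction.

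Second, the 12-month model is not settled, because crossover will change it. This stands, and it is why Case B is shown beside Case A. The larger figures need all three visits in one model.

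Third, the correlations are assumed. This stands. If they are equal at all visits, nothing is lost. The sample size section applies a baseline-to-post SD of change to the 3-month endpoint; with equal SDs, equal change SDs would mean equal correlations at post and 3 months. The document does not show that they are equal, but a falling correlation is only likely, not established.

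Fourth, a reader might infer that the interaction would repair the bias the Discussion fears. The documents do not support that. If knowing the allocation alters reported baseline scores, regression on those scores need not be the right correction, whatever the slope. The interaction makes the adjustment complete only in the ordinary covariate-adjustment sense.

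**Conclusion.** The point holds as a minor one. The listed models use one baseline slope per model. If correlations differ between visits, early effects are under-adjusted and late ones over-adjusted, so the promise to control for baseline differences is kept only incompletely. The size is that of Case A if three visits are pooled and of Case B if 12 months is separate, always under assumed correlations apart from 0.732.

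A reader might go further and infer three things that do not follow:
- **The arm effects are biased.** They are not on average when baselines are balanced; what remains is a fraction of whatever difference exists.
- **Published intervals will be clearly too wide for want of this term.** The reported SE barely moves when it is added alone.
- **The primary result is at risk.** The 3-month EDE-Q contrast loses under 1% in SE in every scenario shown and keeps at most about 8% of a baseline difference. The sample size stands.

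**What to change.** In the statistical analysis plan, add baseline value × time (factor) to the fixed effects of every repeated-measures model that pools two or more follow-up visits, and report the arm contrast at each visit from that model. State which visits enter each model, including how 12 months is handled under crossover. Allow residual variances to differ by visit as well, so that the reported intervals reflect the precision at each visit.

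The interaction costs one degree of freedom for two pooled visits and two for three; the visit-specific variances add as few parameters. No new data are needed and the sample size does not change. The plan is to be completed before database lock, so this can be fixed before results are known.
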